### Relevant concomitant care permitted or prohibited during the trial {11d}

No concomitant care or interventions are prohibited during the trial.

### Provisions for post-trial care {30}

There are no plans for any sort of provision for post-trial care. The last scheduled intervention visit occurs at approximately 18 months post-randomization. It is expected that healthcare providers who deliver the intervention will specify the need for additional WCC post-intervention for each child randomized to the intervention arm of the trial.

### Outcomes {12}

Primary outcomes were selected based on the hypothesized mechanism of effect for the intervention, importance to our target population, and published literature on group WCC in other populations.

#### Primary outcomes

*WCC engagement*: measured as both utilization and experience of WCC.*WCC utilization*: The total number of age-appropriate WCC visits during the 18-month study period will be abstracted from the pediatric electronic medical record (EMR). Adequacy of WCC during this time will be dichotomized as “adequate” (completes the recommended number of WCC visits) or “inadequate” (does not complete the recommended number of WCC visits). This definition is adapted from the Health Plan Employer Data and Information Set (HEDIS) measure for WCC [20]. The mean number of age-appropriate WCC visits during the 18-month study period and the proportion of participants with adequate WCC over the 18-month study period will be compared between the 2 study arms.*WCC experience*: The *Promoting Healthy Development Survey* (PHDS) [21], a 43-item standardized, validated parent survey designed to measure the quality and content of care for children 3–48 months, is completed by participants at the 6-, 12-, and 18-month follow-up assessment visits. The PHDS will be used to evaluate participants’ perceptions of their child’s WCC, including (1) anticipatory guidance—whether the mother received age-appropriate guidance; (2) developmental surveillance—whether the mother was asked about concerns about her child’s learning, development, or behavior, and if concerns were addressed; (3) family-centeredness—whether the mother felt her perspective was heard and valued; (4) family risk assessment—whether the mother was asked about issues in the family (e.g., substance use, emotional support); and (5) helpfulness of care—how helpful the care provided was in specific aspects of parenting (e.g., understanding child behavior). Multiple survey items are used to calculate a score for each component of care evaluated and these composite measures have been previously tested for internal consistency. The mean score for each component of care at each time point will be compared between the 2 study arms.*Parenting knowledge*: The medical literature was reviewed for previously validated questions used to assess parental knowledge about the care and development of intrauterine opioid-exposed infants; no prior questions were identified. Therefore, a survey instrument includes investigator-developed questions specific to this area, (e.g., “Breastfeeding increases the chance your baby will have opioid withdrawal symptoms: Agree/Disagree/Not Sure”), as well as questions from the Knowledge of Infant Development Inventory (KIDI) [22]. The KIDI is a widely used measure of parenting knowledge designed as a diagnostic tool for high-risk parents. The KIDI consists of 58 items grouped into four categories (norms and milestones, principles, parenting, and health and safety) that tests mothers’ knowledge of children’s development and parenting of children from birth through 36 months of age. Items are measured on a 5-point Likert scale with higher scores indicating correct knowledge and developmentally appropriate expectations. In addition to a total knowledge score calculated by summing the number of correct items and calculating an average, four KIDI subscale scores and a knowledge of infant opioid exposure score will also be generated. The total and subscale score at 18 months will be compared between the 2 study arms. The mean change in scores from baseline to 18 months follow-up will be compared between the two study arms.*Maternal-child interaction quality*: This is directly assessed using video-recorded mother/child free play at an 18-month follow-up assessment visit. Interactions are coded by certified scorers using the Keys to Interactive Parenting Scale (KIPS) [23]. KIPS assesses 12 parenting behaviors using quality ratings ranging from 1 to 5 within three domains sub-scale domains: building relationships, promoting learning engagement in language experiences, and supporting confidence. A total score is generated by summing the 12 items and calculating an average to indicate low, moderate, and high-quality parenting behavior. The total and subscale score at 18 months will be compared between the 2 study arms.

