### Participant timeline {13}

### Sample size {14}

Assuming 150 births in the opioid treatment program over an 18-month recruitment period, > 90% rate of maternal legal guardianship at birth, 80% study participation rate, and equivalent group allocation (50%), we expect to enroll 108 participants (n = 54 per study arm) during the project period. A sample size of 54 per study arm will produce a two-sided 95% CI with a distance from the standardized difference in means between two arms to the limits that are equal to 0.38. Additionally, with a sample size of 54 per study arm, a two-sided test for the time-averaged difference between two means in a repeated measures design with a significance level of 0.05 will have 80% power to detect a standardized difference in means of 0.43 in a design with 4 repeated-measurements taken over the 18-month period and with between level correlations of 0.5. A sample size of 54 per study arm will give us 80% power to detect a standardized difference in means of 0.54 (effect size) between two arms using a two-sided two-sample t-test with a significance level of 0.05. Of note, we were unable to find reported data about the cluster effect of different birth months. However, we expect only a negligible cluster effect for birth-month, and so assumed no to negligible intra-cluster correlation coefficient (ICC; 0 to 0.05) to perform the power calculations, which is almost equivalent to performing simple random sampling. However, we preferred the design of cluster random sampling to simple random sampling to account for the effect of birth-month if there is any.

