## Statistical methods

### Statistical methods for primary and secondary outcomes {20a}

#### Quantitative data

Analyses will follow intent-to-treat principles, with participants analyzed according to randomized treatment assignment of the cluster in which they reside. Most analyses will use the individual participant as the unit of analysis, but because randomization is at the cluster level, model-based approaches that account for the correlation between individual participants within a cluster will be used.

Collected data will be summarized in tabular and graphic forms. Demographics and other study variables will be summarized by treatment groups. Mean (SD) or median (interquartile), as appropriate, will be used to describe numerical data, and frequency and percentage will be used to describe the distribution of categorical variables between treatment groups. Two-sample t-test, Mann–Whitney U test, chi-square test, and Fisher’s exact test will be used to compare the distribution of study variables between two-intervention groups as appropriate. Longitudinally collected data will be summarized by intervention groups and data collection time points.

Analysis of variance (ANOVA) and generalized linear and logistic regression models will be used to analyze outcomes measured at one time point, as appropriate. Trajectories of change for outcomes that are repeatedly measured over time will be examined using generalized linear mixed models (GLMMs) and linear, logistic, and negative binomial/Poisson regression models for continuous, binary, and count outcomes. Total scores and subscales from assessments will be used when applicable. The use of GLMM models will allow for an estimation of between-group differences in outcomes at each time point of measurement and will allow for an estimation of changes over time and time by group interactions while accounting for within-subject associations arising from the repeated measures. Clustering of participants will be accounted for in the GLMMs models by including cluster as a random or fixed effect and in the generalized models by using robust variance estimates. Potential covariates will be selected based on consideration of study arm balance and potential confounders for an outcome previously reported in the literature.

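### Parenting knowledge, a primary outcome, is compared twice (raw 18-month score and change from baseline), with neither ranked and no adjustment for the baseline score fixed in advance

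*Protocol article*

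**What the plan says.** Protocol article, Primary outcomes, defines a total KIDI knowledge score and adds that "four KIDI subscale scores and a knowledge of infant opioid exposure score will also be generated". That makes six scores: one total, four subscales and one opioid-exposure score. Two between-arm comparisons are then set out:

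- The first concerns the scores as they stand at the end of follow-up: "The total and subscale score at 18 months will be compared between the 2 study arms".
- The second, in the next sentence, concerns how far each mother has moved since enrollment: "The mean change in scores from baseline to 18 months follow-up will be compared between the two study arms".

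Neither is called the main one.

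The section Quantitative data offers ANOVA and generalized linear or logistic models for outcomes measured once. For repeated outcomes it offers mixed models that give arm differences at each time, changes over time and time-by-arm terms. The baseline value of the outcome is not named as a covariate. The rule for covariates is: "Potential covariates will be selected based on consideration of study arm balance and potential confounders for an outcome previously reported in the literature". The statistical methods also plan a Benjamini–Hochberg adjustment for multiple testing.

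Sample size {14} bases the single-time-point calculation on a comparison without baseline: "A sample size of 54 per study arm will give us 80% power to detect a standardized difference in means of 0.54". The method named for that calculation makes no use of a covariate: "using a two-sided two-sample t-test with a significance level of 0.05".

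**The concern.** Under randomization, the raw 18-month difference and the difference in change have the same expected value: the effect of arm on knowledge at 18 months. In a sample of 108 they will differ by chance, because any baseline difference between the arms passes into one and is subtracted in full from the other. If one favours group care clearly and the other does not, the protocol does not say which is the answer for this primary outcome.

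Neither makes the best use of the baseline. The raw comparison gives the baseline score a coefficient of 0 and the change score gives it a coefficient of 1. A regression on baseline estimates that coefficient from the data.

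The baseline is well suited to adjustment. It is measured at the enrollment visit, and Trial design {8} conceals allocation from participants until that visit is complete, or until delivery for those enrolled while pregnant. What is at stake is precision on a primary outcome in a fixed sample, and a single answer that is known beforehand.

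**Working it through.** **Inputs.** 54 per arm, 80% power, two-sided alpha 0.05, standardized difference 0.54 (Sample size {14}). The ICC range comes from the same section: "assumed no to negligible intra-cluster correlation coefficient (ICC; 0 to 0.05) to perform the power calculations". There are 26 clusters and 108 dyads (Trial design {8}). The baseline-to-18-month KIDI correlation r is not given. The nearest figure is for a design with "4 repeated-measurements taken over the 18-month period and with between level correlations of 0.5", which is a generic value for repeated measurements. So r is an assumption here and a range is shown.

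**Reproducing the plan's figure.** Detectable difference = (1.960 + 0.842) × √(2/54) = 0.539. Power at 0.54 is 80.1% by the normal approximation. By the exact t-test, power is 79.4% and the detectable difference 0.544. The stated figure holds.

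**Variance relative to the raw 18-month comparison**, with equal SDs at both times:

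- raw score: 1
- change score: 2(1 − r)
- baseline-adjusted: 1 − r²

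Raw minus adjusted is r². Change minus adjusted is 2(1 − r) − (1 − r²) = (1 − r)². Both are positive for any r strictly between 0 and 1, so the direction of the gain does not depend on the assumed r.

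**Size of the gain.** Detectable difference = 0.54 × √(variance ratio), ignoring clustering:

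| r | Raw | Change | Adjusted | Power at 0.54 (raw / change / adjusted) |
|---|---|---|---|---|
| 0.3 | 0.54 | 0.54 × √1.4 = 0.64 | 0.54 × √0.91 = 0.515 | 80 / 66 / 84% |
| 0.5 | 0.54 | 0.54 × √1.0 = 0.54 | 0.54 × √0.75 = 0.47 | 80 / 80 / 90% |
| 0.7 | 0.54 | 0.54 × √0.6 = 0.42 | 0.54 × √0.51 = 0.39 | 80 / 95 / 98% |

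Below r = 0.5 the change score is worse than the raw score. At r = 0.5 it is no better. At r = 0.5, 80% power for 0.54 needs 54 per arm raw or change, and 41 adjusted.

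**With clustering at the upper ICC.** Design effect = 1 + (108/26 − 1) × 0.05 = 1.16, applied equally to all three analyses as an approximation. At r = 0.5, power is 74% raw, 74% change and 85% adjusted.

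**Number of tests.** Six scores × two comparisons gives up to 12 tests; one model per score gives six. For a single score the two test statistics have correlation √((1 − r)/2), which is 0.59, 0.50 and 0.39 at r = 0.3, 0.5 and 0.7. The chance under the null that at least one of the two has p < 0.05 is then 8.8%, 9.1% and 9.4%, before any Benjamini–Hochberg adjustment.

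**The case against.** The strongest reply is that the outcomes section only lists what will be summarized, that models belong to the statistical methods, and that an article leaves covariate detail to an analysis plan which may well settle this. In part that stands: an unseen plan could fix the model. But the two comparisons are stated in the article itself, unranked, and a plan that follows it inherits both.

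A second reply is that a mixed model with time-by-arm terms gives both contrasts from one fit. It does. With complete data, though, a model that treats baseline as an outcome and leaves its arm means unconstrained returns the same raw and change contrasts, so the precision is not recovered.

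A third is that Benjamini–Hochberg is planned. It is, and it addresses multiplicity, but it does not rank two estimates of one effect.

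Some stronger readings are tempting and are not supported:

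- A reader might infer that baseline could enter only after a look at arm balance. The covariate rule also admits confounders reported in the literature, so baseline could enter that way; it is simply not fixed.
- A reader might take 0.5 as the plan's KIDI correlation, and so take 1/0.75 = 1.33, a third more participants, as a firm figure. It is illustrative.
- A reader might infer that twice the tests means twice the error rate. The two tests are correlated and an adjustment is planned.
- A reader might infer that randomizing only 26 clusters makes large baseline imbalance likely. At ICC up to 0.05 the SD of a chance difference rises by at most about 8% (√1.16 = 1.08) over individual randomization.
- A reader might extend the point to the secondary scales. Their outcome paragraphs list follow-up times and no baseline.

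**Conclusion.** The point holds in limited form. The article fixes two unranked comparisons of the same primary scores and does not fix baseline adjustment. The change score does use the baseline, but less efficiently than adjustment does. That adjustment is more precise than both follows from the variance formulas, given equal SDs at the two times and r between 0 and 1. How much is gained rests on an assumed r. Against the raw score the detectable difference falls from 0.54 to between 0.515 (r = 0.3) and 0.39 (r = 0.7). Against the change score it falls from 0.64 to 0.515 at r = 0.3 and from 0.42 to 0.39 at r = 0.7. These figures ignore clustering and assume all 54 per arm contribute data. The plan's own power statement is correct for the unadjusted test it describes. This should be corrected, but it does not make either planned comparison invalid.

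**What to change.** For each knowledge score, with the KIDI total leading, name one main analysis: a regression of the 18-month score on arm and the baseline value of that score, accounting for birth-month cluster. Enrollment stage (pregnant or already parenting) may be added as a prespecified covariate. It is defined for every participant, whereas infant age at enrollment is undefined for those enrolled while pregnant. Report raw 18-month means and mean changes by arm as description, without separate tests. Replace selection of covariates by observed arm balance with a list fixed before outcomes are seen by arm. Benjamini–Hochberg can stay, applied to six knowledge tests instead of up to 12.

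The cost is a change of wording in the protocol or analysis plan. The baseline scores needed are those the planned change comparison already requires.

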### Concealment mechanism {16b}

As an open-label study, both participants and researchers know about the assignment of participants to the treatment groups. The treatment assignment sequence was forwarded to the principal investigator of the project after generation.

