### Implementation {16c}

The project statistician generated the treatment assignment sequence. The research coordinator informs participants to their allocation.

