## Assignment of interventions: blinding

### Who will be blinded {17a}

Due to the nature of the study, participants and the investigator responsible for delivering group WCC are not blinded to group allocation. However, all participants are assigned a unique identification number at enrollment to ensure that research personnel responsible for analysis will be blinded to allocation status.

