## Data collection and management

### Plans for assessment and collection of outcomes {18a}

Data is derived through EMR abstraction and from questionnaires completed during study assessment visits. Data from all sources are matched by the participant’s unique study identification number and entered into one master electronic REDCap database. Data entry and checking is an ongoing process as the data become available. The final analytic dataset will be void of personal identifiers to protect the confidentiality of participants.*Medical record abstraction*: EMR data of participants and their children are abstracted by research personnel following participant enrollment into the study, the birth of a participant’s child, and at the 6-, 12-, and 18-month study visits. A standard data abstraction form is used.*Participant assessments*: All randomized study participants in both study arms will have a total of 5 assessment visits with research personnel. The first visits will occur immediately following enrollment into the study (baseline). For participants who enroll while pregnant, subsequent study assessment visits will occur prior to the participant’s child turning 1 month of age, and within 4 weeks of the participant’s child turning 6, 12, and 18 months of age. For participants who are not pregnant when they enroll, subsequent study assessment visits will occur at 1, 6, 12, and 18 months post-enrollment. At each assessment visit, participants will complete a set of standardized questionnaires in a private research room using traditional paper-and-pencil forms. No personally identifying information will be collected on the questionnaires. The 18-month study visit will also involve a 15-min observed free play session between the mother and child, which will be videotaped and subsequently coded according to standardized procedures using the *Keys to Interactive Parenting Scale* [23].*In-depth interviews*: Participants in the intervention arm will participate in semi-structured, individual in-person interviews at 9 and 18 months after their first group WCC session. These interviews will be conducted in a private research room, last 20–30 min, and be audio recorded and transcribed verbatim by a HIPAA compliant transcription service. During the session, participants will be asked to discuss things that they like and dislike about the group WCC program and how the program could be improved. Participants will be asked to report their experiences of receiving care in a group format, focusing on session structure, interaction with other mothers, and receiving specific information. Standardized interview question guides with prompts to engage participants in a fluid discussion will be used.

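### The protocol makes no provision for masking the scorers of KIPS, its only observer-rated primary outcome, although they work later from recorded video

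*Protocol article*

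**What the plan says.** The Primary outcomes section describes maternal-child interaction quality: "This is directly assessed using video-recorded mother/child free play at an 18-month follow-up assessment visit". On scoring it says: "Interactions are coded by certified scorers using the Keys to Interactive Parenting Scale (KIPS". The scale is a matter of graded judgement: "KIPS assesses 12 parenting behaviors using quality ratings ranging from 1 to 5". Plans for assessment and collection of outcomes {18a} adds that the session is one "which will be videotaped and subsequently coded according to standardized procedures", so rating is separate from the visit.

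Two sections deal with who knows the arm. Concealment mechanism {16b} calls the study open-label and says that "both participants and researchers know about the assignment of participants to the treatment groups". Who will be blinded {17a} lists participants and the investigator who delivers group care as not blinded. It then says that each participant gets an ID number "to ensure that research personnel responsible for analysis will be blinded to allocation status". Neither section mentions the KIPS scorers or any other outcome assessor.

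The remaining primary outcomes are not observer ratings. Visit counts come from the medical record, and care experience and parenting knowledge come from questionnaires that the mothers complete.

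**The concern.** Mothers know their arm, so the questionnaire outcomes cannot be masked. KIPS is the one primary outcome where parenting is observed directly, and it can be masked even though care is open-label, because scoring happens later from a recording. It is also the kind of measure in which a rater's expectation can enter: 12 behaviours, each graded from 1 to 5. The Trial design {8} section states the expected direction, namely greater maternal responsiveness in the intervention arm.

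Read as written, the default in {16b} is that researchers know the assignment. The single exception in {17a} is for analysis, and scorers are not named in it. If scorers did know the arm, a modest difference in KIPS would be open to the reply that it reflects the raters and not the mothers. That would weaken the trial's only direct evidence on parenting behaviour.

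**Working it through.** **1. Does any section mask the scorers?**
- Primary outcomes: scorers are certified; masking is not mentioned.
- {18a}: coding is standardised and done after the visit; masking is not mentioned.
- {16b}: researchers know the assignment.
- {17a}: analysis personnel are blinded; scorers appear on neither the blinded nor the unblinded side.
- Confidentiality {27}: study IDs are used on instruments, and names are left out of coded video data. This protects identity; it does not address allocation.

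So no section provides masking of scorers, and no section says that they are unmasked.

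**2. Would the ID number do the job by itself?** A video shows the mother. The trial has one site and 108 dyads. Research personnel see each participant at five assessment visits ({18a}), the research coordinator tells participants their allocation ({16c}), and only intervention-arm mothers are interviewed about group care ({18a}). No section bars any of these staff from scoring. For a scorer who knows the participant, the ID hides nothing.

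**3. The plan's own figure.** Sample size {14} gives 54 per arm, a two-sided two-sample t-test at 0.05 and 80% power at 0.54 SD. This is the calculation that fits KIPS, which is measured once.
- Standard error of the standardised difference: √(2/54) = 0.192.
- Normal approximation: Φ(0.54/0.192 − 1.96) = 80.1%. Exact noncentral t: 79.4%.

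The stated figure reproduces.

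**4. Illustration of what is at stake.** Assume that the true effect is zero, that ratings drift by b SD towards the intervention, that all 54 per arm are scored, that there is no clustering and that KIPS is tested alone at 0.05. The drift b is an assumption; the documents give none. The rejection probability is Φ(b/0.192 − 1.96) + Φ(−b/0.192 − 1.96).

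| Drift b (SD) | b/0.192 | Normal approximation | Noncentral t, 106 df |
|---|---|---|---|
| 0 | 0 | 5.0% | 5.0% |
| 0.1 | 0.52 | 8.1% | 8.1% |
| 0.2 | 1.04 | 18.0% | 17.8% |
| 0.3 | 1.56 | 34.4% | 33.9% |

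A drift of 0.2 SD is 0.2/0.54 = 37% of the difference that the trial is sized to detect.

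**5. How the figure moves under other assumptions, at b = 0.2 (noncentral t).**
- 43 per arm (about 80% of 54 retained, assumed): 15.0%.
- 54 per arm at a threshold of 0.05/4 = 0.0125, the strictest Benjamini–Hochberg step if four tests were adjusted (an illustrative number of tests): 7.0%. The nominal rate there is 1.25%, so the ratio is 7.0/1.25 = 5.6, against 17.8/5.0 = 3.6 in the unadjusted case.

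**The case against.** The strongest reply is that this is silence in a condensed article. Coder assignment, video labels and scoring order often sit in a scoring manual or the full protocol, which is not shown. The scorers are not on the list of unblinded people in {17a}, that section qualifies the broad line in {16b}, and analysis could be read to include video coding. Study IDs are already in use.

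Part of this stands. A reader might infer that scoring is known to be unmasked; the documents do not say so. But the article does address blinding, in a section devoted to it, and its two statements sit awkwardly together without settling the scorers' status. Even on the generous reading of analysis, the only device named is an ID number, which does not mask a face on video.

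Two further inferences should not be drawn.
- A reader might conclude that the blinding of analysts fails, because "The project statistician generated the treatment assignment sequence" and because attendance and group size enter models. No section says that this statistician runs the analysis, and those variables appear only under additional analyses {20b}. The failure is not established.
- A reader might ask for a change of filming room. Nothing suggests that the two arms are filmed in different places.

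It is also fair that the drift sizes are assumed, that the main illustration ignores dropout and the Benjamini–Hochberg adjustment, and that an observed effect near 0.54 SD would be well above a 0.2 SD drift. The illustration shows that a modest drift would matter. It does not show that one will occur.

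**Conclusion.** The point holds in this form: the protocol provides no masking of the KIPS scorers, {16b} and {17a} do not settle whether they know the arm, and the one device named would not hide the arm from a scorer who knows the participant. This leaves the only observer-rated primary outcome open to rater expectation.

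The size cannot be derived from the documents. Under the assumptions in the working, a drift of 0.1 to 0.3 SD would raise the false-positive rate from 5% to between about 8% and 34%. Dropout or multiplicity adjustment would lower these figures. The sample size is not affected. This should be corrected, because KIPS carries the trial's direct evidence on parenting and the remedy is within reach.

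**What to change.** Reconcile Concealment mechanism {16b} with Who will be blinded {17a}, so that it is clear which researchers know the assignment and which do not. In {17a} and in the KIPS paragraph under Primary outcomes, state that the scorers:

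- are masked to arm and cluster;
- receive videos labelled only with a random code;
- rate them in an order that mixes the arms;
- have no role in delivering group care or in telling participants their allocation.

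The cost is protocol wording, relabelling of video files and a shuffled scoring list. That this is cheap is an inference: recordings, IDs and certified scorers are already planned, but no section gives a cost. There are two downsides. Masking may be imperfect if a mother mentions the group on video, and mixing the order may delay some scoring, since recruitment runs over 18 months. Sample size, visits and care do not change.
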